**[name]**

## **Background and Rationale:**

This study and the hypotheses to be tested arise from work done in our group evaluating brain cortical changes in people with chronic back pain. These studies demonstrated a loss of about 1.5 cc of neocortical gray matter per every year of living with the condition ([name] et al.

2004). This gray matter loss is in addition to the 2.5 cc of gray matter loss per year that is a consequence of normal aging. Since this original publication, more than ten studies have replicated the basic result and showed that distinct chronic pain conditions are associated with specific brain anatomical reorganization, characterized by brain regional decrease in grey matter density. Two recent studies have also shown that when the chronic pain is completely reversed the brain anatomical changes seem to at least partially reverse (Oberman et al. 2010, Raecke et al. 2009), within the time span of 4-12 months. The latter two studies provide evidence for a time window for brain anatomical reversal of grey matter abnormalities as well as an estimate of the number of subjects needed to detect such changes. However, they are based on populations where the pain condition is completely eliminated.

The latest advances suggest that this project is eminently possible and provide clear guidelines for its implementation. This proposal has not been submitted elsewhere and is not part of any other project.

A fundamental question that arises from these studies is the extent of reversibility of the brain atrophy associated with chronic pain following continuous use of an analgesic. [name]'s lab has generated very strong evidence (submitted for publication) that the brain anatomy of subjects with OA is dramatically different from healthy subjects. Given that recent data show that joint replacement (in hip OA) reverses brain atrophy, we can now hypothesize with greater confidence that an effective analgesic should also reverse at least some of the brain atrophy observed in OA. Thus, a study in patients with chronic knee OA treated with duloxetine provides a unique opportunity to answer this question. Since in this study OA patients will have a single new agent for four months, one can directly examine the effects of treatment in relation to progression or regression of brain atrophy. Given the results of recent studies, four months should be an adequate time to study the effects of therapy on brain atrophy (we had originally suspected that one year of treatment was necessary to observe such changes). Moreover, since the subjects can be scanned at entry into the study and then at termination of study, this will provide a within subject contrast for changes in brain atrophy which reduces signal variability and provides the opportunity of relating extent of pain relief to changes in brain atrophy. When the pain is completely relieved, a group of 10 patients has been adequate to demonstrate reversal of brain atrophy (Oberman et al. 2010, Raecke et al. 2009).

The issue of atrophy due to pain in relation to changes due to aging warrants further clarification. In the 4 months of treatment all subjects should have atrophy due to aging, about  $2.5 \text{ cc} \times 0.3 = 0.75 \text{ cc}$ . On the other hand the OA cumulative atrophy over the years seems to be proportional to the number of years a given subject has had the condition. If we assume on average that the mean OA duration is 5 years, then the atrophy due to chronic pain should be about  $1.5 \text{ cc} \times 5 = 6.0 \text{ cc}$ . Therefore, in a subject where the OA pain completely disappears with treatment, that subject has the potential of exhibiting a reduction in atrophy of 6.0 cc minus the increased atrophy due to aging of 0.75 cc. Moreover, we assume that placebo responses will not induce reversal of atrophy because placebo mainly reflects attentional and motivational states of the person. There is likelihood that this assumption may not be true. Even in the latter case as we expect placebo to decrease pain less than the real drug treatment, we should still observe smaller changes in atrophy by placebo.

We consider the brain atrophy in chronic pain as an overall marker of the extent of peripheral, spinal cord, and brain reorganization a subject has developed with living and suffering with the condition. Animal models of chronic neuropathic and inflammatory pain repeatedly show that peripheral and spinal cord nociceptive transmission is dramatically changed, leading to

peripheral and central sensitization. We and others have also shown recently in animals that a few days following peripheral nerve injury one observes morphological changes at the level of individual neurons, where number of spines and dendritic lengths increase together with increases in NMDA/AMPA ratio (Metz et al. 2009). We presume that these cortical changes are the same ones contributing to atrophy in human chronic pain. However, most of underlying mechanisms remain to be uncovered. Humans suffering from chronic pain exhibit a large number of cognitive and emotional deficits. We presume that these deficits are directly related to the brain atrophies discovered in chronic pain conditions. However, unfortunately there are no direct studies linking brain regional atrophies to cognitive abilities in chronic pain. Such preliminary studies are underway in [name]'s lab but the results will not be available for quite a period. Thus, reversing this atrophy would correspond to reversing brain plasticity at multiple levels in the nervous system, and should also correspond to improvements in cognitive and emotional abilities.

### **Hypotheses:**

The primary hypothesis to be tested in the study is that subjects with chronic knee OA treated with Duloxetine over a four-month period will show decreased or arrested brain atrophy compared to subjects treated with placebo.

Secondary hypotheses are that in individual patients there will be a relationship between the magnitude of the analgesic effects of treatment and the magnitude of the change in brain atrophy. It is anticipated that there will be a correlation between pain relief by Duloxetine and changes in brain atrophy, whereas the degree of pain relief by placebo will not correlate with brain atrophy changes.

### **Research Methods:**

#### ***Study Design***

A placebo-controlled trial of **two parts** the first of which includes 20 patients with chronic knee OA that will be single blinded, and the second of which includes 60 patients (different from those included in the first part) with chronic knee OA that will be randomized in a 1:1 ratio to Duloxetine or placebo. The Second part (Phase II) will be started after the first part is completed (Phase I).

The total number of OA subjects, hence, culminates to a total of 80 patients. Subjects that terminate the trial before completion of the final visit and scan will be replaced. An additional cohort of normal subjects will also be studied in parallel during the second phase of the study, to allow evaluation of changes in brain volume over time.

In the first part of the study (phase I), all the participants will be receiving placebo. However this part (phase I) of the study will be single blinded. The participants will not know whether they are receiving placebo or active medication. They will be told that there is a possibility that they receive either medication. The researcher, however, will know that all participants in phase one are receiving placebo.

In the second part of the study (phase II), 60 patients will be recruited and randomized into study drug/placebo in a 1:1 ratio in a double blinded manner where neither the subject nor the researcher will know whether the drug dispensed is active or placebo.

In the **first part** of the study, participants will undergo one high resolution anatomical scan (T1) and one functional scan (a resting scan) in a 3 Tesla magnet. A single scanning session comprised of a 10 minute functional scan (a resting scan) will be done two weeks from the first scan. After finishing this second scan (done two weeks after the initial scan), the participants in part one of the study will have completed their role in the study and will not be asked to show up for any other scans or follow-ups.

For the **second part** (Phase II) of the study, participants entering this part of the study will undergo one initial high-resolution anatomic scan (T1) and one functional scan (a resting scan) in a 3 Tesla magnet. A similar scanning session is then performed at the end of the study (approximately 4 months later).

For all of these scans, the participant only has to lie quietly and remain still in the scanner. Each scanning session (consisting of a total of two 10 minute scans) takes a little under 25 minutes to complete and is considered completely non-invasive. The only discomfort is the requirement that subjects lay still in the scanner for the duration. All patient participants complete a general health questionnaire (PHH), the short form of McGill Pain Questionnaire (sf-MPQ), the Western Ontario and McMaster Osteoarthritis Index (WOMAC), and the Beck Depression Index (BDI) at screening, the time of entry (baseline visit), and at the final scanning visit (visit 5). Only the WOMAC will be completed on interim visits three and four.

Healthy control participants will participate in part two of the study only. They will be asked to complete the PHH only at the screening visit (to make sure that there are no potential physical or mental comorbidities or confounding medications). They will be asked to personally complete the BDI at all visits, and they will have the same number and types of scans as OA participants.

All participants will also have the choice of completing an optional visit at the very end of the study that involves answering questions in an open-ended interview and completing a set of new questionnaires that supplement this interview. OA participants will be asked a series of questions about their chronic pain, mood, medical history, and medical beliefs which, depending upon how detailed their responses are, will last 30 minutes to an hour. After the interview, OA participants will be asked to fill out the Chronic Pain Acceptance Questionnaire (CPAQ), the Pain Sensitivity Questionnaire (PSQ), the Perceived Sensitivity to Medicine Scale (PSM), the Five-Factor Personality Index (NEO-FFI), and the Life Orientation Test, Revised version (LOT-R). Healthy participants will be asked a series of questions, most of which are the same as those for the OA and some of which are different and ask about acute painful experiences instead of chronic pain. There are less questions for healthy participants than OA participants, so depending upon how detailed their responses are, healthy participant interviews will last 20-40 minutes. After the interview, healthy participants will be given the PSQ, PSM, NEO-FFI, and LOT-R.

BDI, MPQ, WOMAC, PainDetect, and Pain Catastrophizing Scale Questionnaires will be filled out in an online format during the visit. The online format is almost identical to the hard copy questioner. The CPAQ, PSQ, PSM, NEO-FFI, and LOT-R will be hard copies and will be kept in participant's study folders. No names will be used, subject ID will be used instead. Moreover, access to the online questionnaires and responses will be password protected and under the

control of the research coordinator. The patient identification, subject randomization, and treatment monitoring, including safety assessment, will be done under direct supervision of [name] (MD, PhD). Study visits will be scheduled as indicated:

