Brain image data collection and analysis is done under [name] supervision, which will be performed double blinded. Brain scan data will be transferred to [name]'s lab where the automated brain morphometric analyses are performed. We contrast brain morphology using a 2-way analysis of variance, factor one is group (patients treated with drug, with placebo, and healthy controls), and factor two is repeat measure time of scan. A secondary analysis will involve correlating brain regional changes to pain (VAS score from sf-MPQ) and the other questionnaire outcomes.

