### ***Study Endpoints***

Primary: Overall neocortical gray matter volume and regional gray matter density in patients treated with Duloxetine and placebo

Secondary: Changes in gray matter volume and regional density measures will be correlated with changes in pain parameters

Exploratory (Optional Visit): Differences in past experience and current expectations, as measured with the open-ended interview, will be

correlated to treatment response and to differences and/or changes seen in brain parameters

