For part two of the study, high-resolution anatomic brain images and functional brain scans are collected before and after four-months of treatment with duloxetine in 30 OA patients, in 30 OA patients who receive placebo, and in 25 healthy controls. Brain morphology is contrasted between these two time points, across the three groups, for overall neocortical gray matter volume and regional gray matter density changes. Pain relief, based on questionnaire outcomes and the MPQ's VAS, are then used as covariates in both patient groups to identify the effect size of magnitude of pain relief on restoration of brain grey matter. The procedures follow exactly our publications on the topic (Geha et al., *Neuron*. 2008; 60: 570. [name] et al., *J. Neuroscience* 24:10410, 2004).

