### ***Statistical Analysis***

As soon as participants' MRIs are collected they are transferred to [name]'s lab where again we check for quality. Final data analysis cannot begin until all the repeat brain scans are collected, where we then follow procedures that we have used in the past. The correlative analyses require also getting all the pain questionnaire and drug use outcomes at study completion.

All participants' scans will be run through a quality control pipeline. Those participants whose scans are returned by the pipeline as poor in quality (e.g, they may have a low signal-to-noise ratio or too much movement), and verified to be so by qualified personnel, will *not* be included in data analysis concerning how the brain changes under the influence of the study drug. However, these participants' questionnaire data, medical history, and pain reportings may still be used in data analysis concerning drug efficacy.

Brain morphometry analysis follows our published procedures (Geha et al., Neuron. 2008; 60: 570. [name] et al., J. Neuroscience 24:10410, 2004). Briefly, we use three approaches to compare brain anatomy between groups (primary hypothesis) and correlate brain anatomical parameters with pain relief in the treatment arm (secondary hypothesis). For all subjects we

calculate whole-brain gray matter volume for the neocortex, normalized by skull size, and corrected for sex and age confounds. In the first approach, this value is then contrasted between treatment and placebo groups, which test the primary hypothesis for the whole-brain. In a second analysis, we perform voxel-based morphometry (VBM) where we calculate gray matter density for each voxel of gray matter (3 mm^3, about 20,000 voxels/brain). The VBM results are corrected for whole-brain volume, age and sex, and then contrasted between the groups. This contrast indicates what specific brain regions have changed in gray matter density and in what direction. In the third approach, we subdivide the neocortical gray matter into 80 morphological sections (Brodmann areas), correct them for age, sex, and whole brain volume, and contrast them between the two groups.

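### Part Two replaces randomised patients who leave before the final scan, so the primary duloxetine–placebo contrast is in effect completers-only and randomisation is not guaranteed to protect it

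*Protocol*

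**What the plan says.** - **Replacement.** Study Design: "Subjects that terminate the trial before completion of the final visit and scan will be replaced". The sentence covers both parts of the study. It matters here for Part Two, where 60 patients are randomised 1:1.
- **Numbers with paired scans.** Study Procedures, Part Two, describes imaging "before and after four-months of treatment with duloxetine in 30 OA patients", with 30 placebo patients and 25 healthy controls alongside.
- **Primary endpoint.** Study Endpoints: "Overall neocortical gray matter volume and regional gray matter density in patients treated with Duloxetine and placebo".
- **Primary analysis.** The Part Two text preceding Study Drug: "We contrast brain morphology using a 2-way analysis of variance", with group and time of scan as factors. Statistical Analysis adds: "Final data analysis cannot begin until all the repeat brain scans are collected".
- **Scan quality.** Under Statistical Analysis, participants whose scans are flagged by the quality pipeline ("they may have a low signal-to-noise ratio or too much movement") and confirmed as poor by staff will *not* "be included in data analysis concerning how the brain changes under the influence of the study drug". For them, "these participants' questionnaire data, medical history, and pain reportings may still be used in data analysis concerning drug efficacy".

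The protocol does not say whether a replaced patient stays in the analysis, how a replacement is allocated, or whether a patient who stops study drug is still asked to come for the final scan.

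**The concern.** The primary outcome needs two scans. A patient who terminates early has no final scan, the vacated place is filled, and the target of 30 + 30 is expressed as patients scanned before and after treatment. Followed as written, the primary contrast compares those who stayed on one arm with those who stayed on the other. Randomisation balances the groups as allocated; it does not balance the subsets who complete.

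Selection is plausible here. Study Drug lists common adverse events that could cause unequal loss, and patients enter with pain of at least 5/10 and a need for daily medication, so lack of relief is also a reason to leave. The secondary hypothesis itself links pain relief to gray-matter change on duloxetine. If loss follows tolerability or relief, and these are related to gray-matter change, both the primary contrast and the pain-relief correlations are exposed.

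Replacement restores the sample size but leaves any such bias in place. A statistical analysis plan could name a missing-data method, but it could not recover final scans that were never sought.

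**Working it through.** **1. The plan's own figure.** Sample Size Considerations takes two earlier studies with n = 10 and triples the drug group: 3 × 10 = 30, and 30 + 30 = 60 at 1:1. This is consistent arithmetic. The section gives no alpha, power, effect size, SD or drop-out rate, so everything below rests on stated assumptions.

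**2. Bias of a completers' contrast.** Let *d* be the fraction lost in an arm and Δ the amount, in SD of gray-matter change, by which leavers do worse than completers. The completers' mean exceeds the mean of all randomised in that arm by *d* × Δ. With a common Δ the bias in the contrast is (d_drug − d_placebo) × Δ.

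| Assumed loss, drug v placebo | Δ = 0.5 SD | Δ = 1.0 SD |
|---|---|---|
| 20% v 10% | 0.10 × 0.5 = 0.05 | 0.10 × 1.0 = 0.10 |
| 30% v 15% | 0.15 × 0.5 = 0.075 | 0.15 × 1.0 = 0.15 |

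The positive sign is an input: it follows from assuming more loss on drug and a deficit in leavers. Reversing the loss rates reverses it.

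**3. Effect on type I error, 30 completers per arm.** SE = √(2/30) = 0.258 SD. With δ = bias/SE, the two-sided error is Φ(−1.96 + δ) + Φ(−1.96 − δ).

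- Bias 0.05: δ = 0.194; 0.0387 + 0.0156 = 5.4%.
- Bias 0.15: δ = 0.581; 0.0839 + 0.0055 = 8.9%.

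**4. Dependence on the loss mechanism.** This was simulated with no true effect, 30 completers per arm after replacement, a t-test at two-sided 0.05 and 8,000 runs per row. Outcome-related leaving acts through a latent variable with correlation ρ to gray-matter change.

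| Assumed loss | Bias (SD) | Type I error |
|---|---|---|
| 20% each arm, unrelated to outcome | 0.00 | about 5% |
| 20% each arm, same mechanism, ρ = 0.5 | 0.00 | about 5% |
| 25% v 10%, same mechanism, ρ = 0.3 | 0.07 | 5.5% |
| 25% v 10%, same mechanism, ρ = 0.5 | 0.12 | 7.5% |
| 25% outcome-related on drug, 10% random on placebo, ρ = 0.5 | 0.21 | 13% |
| 20% each arm, opposite mechanisms, ρ = 0.3 | 0.21 | 13% |
| 20% each arm, opposite mechanisms, ρ = 0.5 | 0.35 | 30% |

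Unequal rates are not required; different reasons for leaving are enough. The last three rows are harsher than step 2 assumes and show sensitivity only. For scale, 30 per arm detects (1.96 + 0.84) × 0.258 ≈ 0.72 SD with 80% power.

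**5. How many would be randomised.** To end with 30 + 30 completers: 30/0.8 + 30/0.9 = 70.8, or 30/0.7 + 30/0.85 = 78.2. About 71 to 78 patients would be randomised, with 11 to 18 of them outside the completers' analysis.

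**The case against.** Replacement is an enrolment rule. The protocol does not say that replaced patients' data are discarded, and analysis sets and missing-data methods are often left to a statistical analysis plan, which is not at hand. Terminating the trial is also not the same as stopping study drug, and nothing bars a patient who has stopped from attending the final scan. This is fair as far as it goes. However, the rule is triggered by the absence of the final visit and scan, the target is counted in paired scans, and nothing asks for a scan after early stopping. A later plan can only model those gaps.

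The scan-quality exclusion is the weaker half. It follows a pipeline flag confirmed by staff, and the protocol says image collection and analysis are blinded. Movement might still relate to treatment or pain, but no difference between arms is shown.

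Four stronger readings are tempting and are not supported:

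- *The bias most likely favours duloxetine.* The secondary hypothesis expects relief to track gray-matter change on drug only, which points that way. But the Background concedes that placebo might also affect atrophy, and less relief is expected on placebo. Loss of placebo non-responders could then improve the placebo completers' mean and push the bias the other way. The adverse-event list gives no discontinuation rates and no link to gray matter.
- *The bias can be stated as a share of the expected effect.* The protocol gives no SD for gray-matter change and says its sample size has no statistical justification, so there is no denominator.
- *Replacements will be steered to the depleted arm.* The text is silent on allocation of replacements, and Part Two is double blind.
- *The number randomised will be hidden.* Nothing limits what will be reported.

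Finally, the Background asks about continuous use of an analgesic, whereas scanning patients off drug addresses a treatment-policy question. That choice deserves a stated justification, but selection among completers is a risk for either question.

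**Conclusion.** The point stands for randomised Part Two: the primary contrast is in effect completers-only, and protection by randomisation is not guaranteed. That is not a demonstration of bias. With no true effect, bias is zero if loss is unrelated to gray-matter change, or has the same rate and mechanism in both arms. Otherwise its direction and size depend on facts the protocol does not give. The illustrative 0.05–0.15 SD, with type I error of about 5.4–9%, rests on the assumed loss rates and leaver deficits shown above.

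The point does not apply to Part One, where all patients receive placebo and nobody is randomised. Because Sample Size Considerations calls the study exploratory, this is a should-fix. The exploratory label does not remove it, since Hypotheses states a primary comparison between the randomised arms.

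**What to change.** For Part Two, state that:

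1. every randomised patient with a baseline scan stays in the primary analysis in the assigned arm, whether or not replaced. A missing or quality-failed final scan is a missing outcome, handled by a likelihood-based model or multiple imputation, with the completers' analysis as a sensitivity analysis;
2. patients who stop study drug but have not withdrawn consent are asked to attend the scheduled Visit 6 scan and questionnaires;
3. any additional patient takes the next number on the randomisation list;
4. numbers randomised, lost and excluded for scan quality are reported by arm.

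Most of this is wording. Item 2 must be in place while patients are being followed, because a missed scan cannot be obtained later. The real cost is some final scans beyond the planned 60 if leavers are both scanned and replaced: at most 11 to 18 under the loss rates assumed above. The estimate may also be smaller than the completers' one.
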